**Methods:**

A cohort design will be used. A representative sample of community-dwelling adults with an SMI, including those in care (*n* = 650) and not in care (*n* = 150), will be followed over time. During a two-year time period, participants will be interviewed twice using a wide-ranging set of validated instruments. Interview data will be matched with administrative data about the care process, as retrieved from their patient files. Primary outcomes are changes over time in recovery, societal participation and quality of life, controlled for the occurrence of adverse life-events during follow-up. Additionally, prevalence estimates of and associations between social functioning, safety and discrimination, substance use and health indicators will be investigated.

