The research program is modular. It consists of multiple interrelated research projects. Each of these projects addresses deinstitutionalization from one of the aforementioned perspectives. The current study protocol applies to the ‘client study’ of the program, that focuses on the perspective on deinstitutionalization from its main stakeholder: community-dwelling adults with an SMI. More specifically, the protocol lays out the study design by means of which a representative research cohort of people with an SMI in Amsterdam will be assembled (i.e. inclusion and exclusion criteria) and followed over time. Additionally, the protocol describes the process of participant recruitment, the instruments that will be administered, the study’s primary outcome measures and the statistical analyses that will be performed. Furthermore, the protocol specifies how the following research questions will be addressed:Which trends in the development of community-dwelling people with an SMI concerning their quality of life, recovery, daily functioning and societal participation can be observed over the course of time?Which needs of community-dwelling people with SMI are most important with respect to their recovery and societal participation?How are these needs addressed and accommodated by formal and informal providers of ambulatory care and support?How can the provision of community-based ambulatory care for people with an SMI be described with respect to treatment compliance, therapeutic alliance and frequency/timeliness of care consults?What is the prevalence and incidence during follow-up of personal crises and escalations, including psychological crises, compulsory (clinical) treatment and victimization, among this population?

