## Methods

### Study design

The Deinstitutionalization Amsterdam Client-study is a cohort study that started in December 2017. The study is planned to include approximately 800 adults with an SMI. The study population is designed to be representative for the target population of community-dwelling adults with an SMI at the city level, the level of the city-districts and the level of the city’s quarters (i.e. combined neighborhoods). To acquire a better insight into developments in the functioning and recovery of community-dwelling adults with an SMI and their associated needs for care/support, a comprehensive set of measurement instruments will be administered twice, with a two-year time interval, by means of semi-structured interviews. Also, the occurrence of adverse life-events during follow-up will be associated with developments in people’s functioning (i.e. social recovery and societal participation) over the course of time. Additionally, information about the care processes during that time will be retrieved from participants’ patient files.

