### Primary study outcomes

The study has three primary outcome measures: recovery, societal participation, and quality of life. With respect to recovery, the total score of the National Recovery Scale [77] will be used. Concerning societal participation, two separate indicators will be involved: 1) having formal work/daytime activities (yes/no) and 2) the total score of the Social Exclusion Index for Health Surveys (SEI-HS) [55]. Last, quality of life will be operationalized according to the total score of the MANSA-16 [72].

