Research question 3 will be analyzed using data from the baseline and follow-up measurement by means of generalized linear mixed models with repeated measurements of recovery, quality of life and societal participation as dependent variables. The time between both measures will be included as a within-subjects factor. The same set of predictor variables as mentioned above will be treated as time-dependent independent variables. Additionally, the total score on Brugha’s life-events questionnaire will be included as a potential mediator to assess the effect of having experienced adverse life-events in the time period between baseline and follow-up on the associations between predictor and outcome variables. All variables will be checked for potential outliers. Missing values will be dealt with appropriately. Participants with > 80% missing values on all items will be deleted from the final dataset. For most measures, descriptive analyses will be carried out and the proportion of missing values will be reported for each variable of interest. In subsequent statistical analyses, values missing at (completely) random (i.e. MAR and MCAR) will be deleted pair wise. Values that are not missing at random (NMAR) will be imputed with either the mean, median or using multiple imputation, whichever is most appropriate. Concerning outcome measures that are a sum score of items, instructions from the instrument developers will be followed (e.g., impute missing values with the mean value of the non-missing items and calculate a sum score only if < 10% of items are missing).

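### No stated model estimates the two-year change that is the primary outcome: question 1 gets a baseline-only regression, and the one model with a time term also adjusts for time-dependent predictors

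*Protocol article*

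**What the plan says.** **Target.** The abstract states: "Primary outcomes are changes over time in recovery, societal participation and quality of life, controlled for the occurrence of adverse life-events during follow-up". In the Background list of research questions, the first asks "Which trends in the development of community-dwelling people with an SMI concerning their quality of life, recovery, daily functioning and societal participation" can be seen as time passes, and mentions no adjustment. Study design justifies two interviews two years apart in similar terms: "To acquire a better insight into developments in the functioning and recovery of community-dwelling adults with an SMI". Primary study outcomes reads "The study has three primary outcome measures: recovery, societal participation, and quality of life" and names four indicators: the National Recovery Scale total, formal work or daytime activities (yes/no), the SEI-HS total and the MANSA-16 total. That section does not say whether levels or changes are meant.

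**Analysis.** Statistical methods attaches question 1 to a regression on baseline data, with unmet needs (CANSAS), discrimination, stigma and victimization as predictors. Descriptive summaries of all study measures are offered as partial answers to questions 2, 4 and 5. The longitudinal analysis follows: "Research question 3 will be analyzed using data from the baseline and follow-up measurement by means of generalized linear mixed models". Its time term is described as: "The time between both measures will be included as a within-subjects factor". On covariates: "The same set of predictor variables as mentioned above will be treated as time-dependent independent variables". The life-events total is added as a potential mediator of the predictor-outcome associations.

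**The concern.** The study's central promise is to show how people fare over two years, but no stated model has that change as its estimate. The baseline regression has no time term. The longitudinal model has one, but conditions it on variables measured at both interviews that may themselves shift. The Background describes discrimination, stigma and victimization as harmful to participation and closely linked to recovery, so they may well move together with the outcomes.

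An analyst who follows the text and looks for the trend finds only this adjusted time coefficient. Read as the trend, it answers a different question: how much the outcome changed apart from what goes with changes in needs, discrimination, stigma and victimization.

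The question labels add to the difficulty. The third question in the Background list concerns how formal and informal providers meet people's needs, not change in the primary outcomes. The text attached to question 1 describes associations with need, not trends.

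**Working it through.** **1. Target against analysis**

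| Place | What it fixes |
|---|---|
| Abstract, Methods | Change over time, controlled for life events |
| Background, question 1 | Trends that can be observed; no adjustment |
| Primary study outcomes | Four indicators; change not mentioned |
| Statistical methods, question 1 | Baseline data only; no time term |
| Statistical methods, question 3 | Time term plus time-dependent predictors plus life events |

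No row in the analysis part is a model with time alone. Life events also have two roles: something to control for in the abstract, and a mediator in Statistical methods.

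**2. What the time coefficient measures**

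The article gives no figure for change that could be reproduced. For a linear outcome, write the model as y = a + tau × time + sum(b_k × x_k) + person effect + error. Taking the mean difference between interviews:

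total change = tau + sum(b_k × mean change in x_k)

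so tau = total change − sum(b_k × mean change in x_k).

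A variable with one fixed value per person has zero change and drops out of the sum. A variable that shifts between interviews does not. The contribution of life events therefore depends on how the score is entered, which the article does not say. For the yes/no indicator the same logic holds on the model's link scale, but the identity is not exact for proportions.

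**3. Range under assumed inputs**

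None of the effects or shifts below comes from the article. The sample size of 800 is the planned one; the article's own inputs give 1739 × 0.33 + 820 × 0.20 + 157 × 0.50 = 573.9 + 164.0 + 78.5 = 816.4, in line with approximately 800. Two waves were simulated with a random intercept, one time-dependent predictor and no direct time effect (tau = 0), with 20 replicates per setting. Brackets show the share of replicates with p < 0.05.

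| b | Rise in x | True total change | Time-only model | Model with x |
|---|---|---|---|---|
| −0.3 | 0 | 0.000 | 0.001 (10%) | 0.002 (15%) |
| −0.3 | 0.1 | −0.030 | −0.028 (20%) | 0.004 (5%) |
| −0.3 | 0.3 | −0.090 | −0.100 (80%) | −0.009 (10%) |
| −0.5 | 0 | 0.000 | 0.013 (10%) | 0.008 (5%) |
| −0.5 | 0.3 | −0.150 | −0.153 (100%) | −0.002 (5%) |
| −0.5 | 0.5 | −0.250 | −0.247 (100%) | 0.003 (15%) |

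The time-only model recovers the total change. The model with x returns about zero, which is the direct effect that was put in. With no shift in x, both estimate the same quantity.

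**4. A direct effect as well**

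With tau = −0.05, b = −0.5 and a rise of 0.3, total change = −0.05 + (−0.5 × 0.3) = −0.20. Sixty simulated data sets of 640 people gave −0.201 (SE 0.039; significant in 98%) from the time-only model and −0.049 (SE 0.034; 28%) from the adjusted one.

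**5. The reverse case**

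If tau = +0.15 and b × change in x = −0.15, the total change is 0 and the adjusted model shows an improvement. The discrepancy can go in either direction.

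**The case against.** Five points can be made for the plan.

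- **The plan never says that the adjusted time coefficient is the trend.** This stands. The longitudinal paragraph is about predictor-outcome associations, and for that purpose time-dependent predictors alongside time are an ordinary choice. A reader might infer that the study's main answer will be wrong; the text supports only that it could be wrong if this coefficient were read as the trend.
- **The primary outcome is not uniformly an unadjusted change.** This stands too. A reader might infer that several sections define it so, but the abstract already conditions on life events, the outcomes section does not mention change, and only the research question speaks of observed trends.
- **Raw levels may be visible.** This stands in part. Descriptives of all study measures are planned and the same instruments are used at both interviews. The explicit promise of baseline and follow-up reporting covers socio-demographic data only, however, and no paired change or interval is specified. Since the labels do not match the question list, the assignment of descriptives to questions 2, 4 and 5 should not be pressed to exclude question 1.
- **The illustrations return their inputs.** This stands. A reader might take from step 4 that three quarters of a decline would vanish, but 0.15/0.20 is fixed by the assumed values and predicts nothing about this cohort.
- **A condensed article may leave model-building to a fuller plan.** This does not dispose of the point. The article does state an analysis for question 1 and one longitudinal model, and neither estimates the change it names as primary.

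**Conclusion.** The point holds as a mismatch between the stated target and the stated analyses. Followed as written, the baseline regression attached to question 1 cannot estimate change, and the only time coefficient available is the change left after removing what runs through the time-dependent variables. Read as the trend, it could understate, hide or even create a change.

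The size in this study cannot be computed. It equals the sum of b_k × mean change in x_k and is zero if the predictors do not shift. Under the assumed inputs in the table, true changes of −0.03 to −0.25 appear as about zero; that range rests on assumed effects of −0.3 and −0.5, shifts of 0.1 to 0.5 and no direct time effect. No causal claim about community living is needed, since the identity is algebraic. The documents do not show that a wrong trend will be reported. They show that the analysis giving the right one is not stated.

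**What to change.** 1. In Statistical methods, state that question 1 is answered, for each of the four primary indicators, by the mean change from interview 1 to interview 2 with a 95% CI, from a mixed model with interview occasion and at most fixed baseline characteristics. For work or daytime activities, report the change in proportion.
2. Keep the model with time-dependent predictors and life events as a secondary, explanatory analysis, and say that its time coefficient is not read as the trend.
3. Correct the research-question labels in Statistical methods so that they match the list in the Background.
4. Give life events one role, and align the abstract's wording on control with the mediator wording in Statistical methods.

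The cost is one simpler model per indicator and some rewording. No new data are needed.

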**Fig. 1 Fig1:**
[figure not shown]
Flowchart of the composition of the target population from which the study population will be sampled

In-care and not-in-care participants were recruited consecutively, to avoid duplicate recruitment attempts. The recruitment period of the in-care group, and the LZA-cohort in parallel, was December 2017–January 2021. Recruitment of participants in the not-in-care group was executed between January 2021 and January 2022. At baseline, participants were interviewed about their functioning with respect to important aspects of life (see instruments) by a pool of trained interviewers. All participants will receive a financial compensation of €15, for each interview. Interview data will be matched with information retrieved from patient files that concerns important aspects of the care process. Follow-up interviews will be held two years after the first interview and will consist of the same set of instruments as administered during interview 1. The recruitment period of follow-up interviews of the in-care cohort and the LZA-cohort will start in December 2019 to end in June 2022. Not-in-care participants will be approached to participate in interview 2 between January and September 2023.

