### Statistical methods

All cross-sectional socio-demographic data from both baseline and follow-up measurements will be reported in terms of percentages, means with standard deviations, and quartiles. In addition, all study measures (from the instruments administered and from the registry data) will be analyzed descriptively to provide estimates of the relevant proportions within our study population with respect to these variables as (partial) answers to research questions 2, 4 and 5.

In addition, to provide information on the association between experienced need, and the primary outcome variables (research question 1), data collected at baseline will be analyzed using multivariate regression with recovery, societal participation and quality of life as separate dependent variables and total scores on the CANSAS (i.e. number of unmet needs for care), discrimination scale, stigma scale and victimization as independent (predictor) variables. Any potential mediating effects on the associations between predictors and outcomes variables will be investigated by adding age, sex, psychiatric symptoms (BPRS-E), harmful/dependent alcohol and/or drug use (AUDIT and DUDIT respectively), physical health (RAND SF-36) and city-districts as covariates in these analyses.

To answer research question 2, relationships between the outcome measures and distinct CANSAS items, registry data concerning the care process (i.e. treatment compliance, therapeutic alliance, frequency and timeliness of care consults and self-reported support for social problems) from mental health institutions and support/welfare organizations will mainly be reported in terms of percentages and, for obvious comparisons between groups, using regression models and chi-squared tests. Their associated proportion of variance explained Nagelkerke’s R^2^, Phi for 2 × 2 tables and Cramer’s V for larger than 2 × 2 tables will be reported. Phi and Cramer’s V will be interpreted as indicating no or very weak (> 0), weak (>.05), moderate (>.10), strong (>.15) or very strong (>.25) association between variables [93]. Eta-squared and Cohen’s D will be interpreted as very small (0–.19), small (.20–. 49), moderate (.50–.79), large (.80–1.20), very large (1.20–1.99) or huge (2.0) [94].

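### The two-wave mixed models, as written, take over the four baseline predictors but not the baseline covariates, leaving the longitudinal associations open to confounding

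*Protocol article*

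**What the plan says.** All of this is in the Protocol article, mostly under Statistical methods.

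- **Baseline regressions.** Recovery, societal participation and quality of life are the dependent variables. The number of unmet needs on the CANSAS is listed with the "discrimination scale, stigma scale and victimization as independent (predictor) variables".
- **Covariates at baseline.** A second group is then introduced: "Any potential mediating effects on the associations between predictors and outcomes variables will be investigated by adding age, sex, psychiatric symptoms (BPRS-E"), followed by harmful or dependent alcohol and drug use, and ending with "physical health (RAND SF-36) and city-districts as covariates in these analyses". The stated purpose is to look for mediation. Confounding is not mentioned.
- **Longitudinal models.** The two-wave analysis uses "generalized linear mixed models with repeated measurements of recovery, quality of life and societal participation as dependent variables". On the explanatory side it says: "The same set of predictor variables as mentioned above will be treated as time-dependent independent variables". One further term is named: "the total score on Brugha’s life-events questionnaire will be included as a potential mediator".
- **Data at both waves.** Under Participants, after Figure 1, the follow-up interviews "will consist of the same set of instruments as administered during interview 1".
- **Abstract.** For change in the primary outcomes, adverse life events are the only control named.

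**The concern.** The protocol sets out a fuller list of terms for its cross-sectional models than for the models that address change in its primary outcomes. Self-rated need, perceived discrimination and stigma may all move with symptom severity, and so may recovery and quality of life. Someone whose symptoms worsen between interviews could report more unmet need and more stigma together with lower recovery. A model without symptoms would credit that joint movement to need or stigma. A random intercept does not by itself prevent this: it removes neither confounding by something that changes over time nor, in general, confounding between persons.

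Age, sex and district raise a simpler issue. They are background characteristics and cannot plausibly be mediators of need or stigma, so nothing is gained by leaving them out. The Bias section itself says that socio-economic and background characteristics vary between quarters, which is a reason to account for area.

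**Working it through.** There is no stated figure to reproduce, so the first step is a comparison of wording.

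**1. Which terms are named for which model**

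| Term | Baseline regressions | Two-wave mixed models |
|---|---|---|
| CANSAS unmet needs, discrimination, stigma, victimization | yes, as predictors | yes, as time-dependent terms |
| Age, sex, city-district | yes, as covariates | not named |
| BPRS-E, AUDIT/DUDIT, SF-36 | yes, as covariates | not named |
| Life events | not named | yes, as potential mediator |

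**2. Could the carried-over set mean the whole baseline list?** Two details point the other way. The protocol applies the word predictor to the first row only, and uses covariate for the next two. It also says the carried-over set is treated as time-dependent, which suits the four predictors but not sex, and suits age only through elapsed time. The Abstract, with life events as its sole control, agrees with the narrow reading. No sentence excludes the covariates, however.

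**3. How large could the effect be?** The protocol gives no correlations or effect sizes, so every input here is an assumption. On standardised variables, with true predictor slope b, symptom-outcome effect g and predictor-symptom correlation r:

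slope without symptoms = b + g × r, so shift = g × r

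| g | r | shift | slope if b = -0.20 |
|---|---|---|---|
| 0 | any | 0 | -0.20 |
| -0.1 | 0.2 | -0.02 | -0.22 |
| -0.3 | 0.2 | -0.06 | -0.26 |
| -0.3 | 0.4 | -0.12 | -0.32 |
| -0.5 | 0.6 | -0.30 | -0.50 |

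The shift is zero if either g or r is zero.

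**4. Simulation check.** Further assumptions: 800 people seen at both waves without dropout, one predictor, the same correlation r between and within persons, 60% of predictor and symptom variance between persons, and random-intercept and error variances of 0.5 each. The model was fitted by generalised least squares with known variance components. The true predictor effect was zero and the standard error about 0.026.

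| r | g | g × r | simulated slope, symptoms omitted | rejections at 5% |
|---|---|---|---|---|
| 0.2 | -0.2 | -0.04 | about -0.04 | 34% |
| 0.3 | -0.3 | -0.09 | about -0.09 | 91% |
| 0.5 | -0.3 | -0.15 | about -0.15 | 100% |

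With symptoms in the model the slope averaged about zero, with 4 to 6% rejections. The simulation builds symptoms in as a pure confounder, so it shows what would follow if they were one. It is not evidence that they are.

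**The case against.** The strongest reply is that the protocol gives these variables a mediator role. If need or stigma worsens symptoms and symptoms then lower recovery, a model without BPRS-E estimates a total effect, and the shift computed above is an indirect effect and not bias. This stands for BPRS-E, substance use and physical health. It does not help for age, sex and district. Nor does it support leaving the scores out altogether, since examining mediation also needs models with and without them.

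A second reply is that a condensed article may leave the full covariate list to another document, and that the carried-over set could be meant loosely. That is possible. But this article does list terms for both models, and the lists differ, so the text needs settling whichever was intended.

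A reader might go further in four ways that the document does not support.

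- **That the longitudinal associations are confounded by symptom severity.** No figure in the protocol shows this, and the sizes above rest wholly on assumed inputs.
- **That the conclusion about which needs matter for recovery depends on these models.** That is research question 2, which is handled separately with distinct CANSAS items. The mixed model uses the number of unmet needs and cannot rank individual needs.
- **That baseline and longitudinal coefficients cannot be compared.** The covariates are added to the baseline regressions, so a baseline model with the same four predictors is available, apart from the life-events term.
- **That only a symptom-adjusted model should carry the conclusions.** The CANSAS has a psychological wellbeing domain, so conditioning on same-wave symptoms may over-adjust.

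**Conclusion.** The point holds as a gap in the specification. As written, the mixed models contain four predictors and life events. Age, sex, city-district, BPRS-E, AUDIT/DUDIT and SF-36, which the baseline regressions use, are not carried over. This leaves the longitudinal associations open to confounding, including by symptom severity. The size cannot be derived from the document: under the assumed ranges the shift in a standardised slope runs from none to -0.30, and whether it is bias or an indirect effect depends on a causal role that the protocol has not fixed for the mixed models. The case is clearest for age, sex and district. For the symptom, substance-use and physical-health scores, the supportable request is to show both versions and declare their roles. It is worth correcting because it is cheap and concerns the models for the primary outcomes.

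**What to change.** In the mixed-model paragraph of Statistical methods:

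- enter age, sex and city-district as fixed covariates in every mixed model;
- report each model both without and with BPRS-E, AUDIT, DUDIT and SF-36, measured at each wave;
- state in advance, for each of these variables, whether it is treated as a confounder or a mediator, and which model is primary.

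The cost is a short addition to the text and extra model runs for each outcome. No new data are needed, because the interview instruments are repeated at follow-up. The downside is small: same-wave symptoms may lie partly on the path from need or stigma to the outcome, so the fully adjusted coefficients may be conservative and should be read beside the less adjusted ones.

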With respect to the in-care and not-in-care cohorts, their relative proportions within the total SMI-population in Amsterdam are approximately 76 and 24%, respectively [30]. Furthermore, around 90% of both groups lives independently (i.e. community dwelling). In-care participants will be recruited at the two largest mental health care providers in Amsterdam, Arkin and GGZ inGeest. Together, these organizations are estimated to provide care/treatment to two thirds of the total in-care population of people with an SMI in Amsterdam [39]. The remaining 33% of the in-care SMI-population, those who receive mental health care from one of several other (small) providers, will not be included as we expect to obtain a representative sample of the in-care population from the selected service providers. Moreover, recruiting participants at numerous care providers would require a disproportional effort and is therefore considered unfeasible. The ‘not-in-care’ participants will be recruited at a variety of social welfare and social support organizations in Amsterdam, including organizations that target the homeless (e.g., HVO-Querido, Leger des Heils, Cordaan, Volksbond). In this group, the SMI-criteria will be assessed during the interview.

As such, on the basis of 1) the assumed average SMI prevalence of 1.6% among the adult population of the selected quarters (237,157 * 1,6% = 3795 people), and 2) the proportion of adults with an SMI who are registered as a mental health care patient (76%, *n* = 2884), and 3) of whom at one of the two main mental health care providers in the city (66%, *n* = 1903) and 4) the proportion within this group who live independently (i.e. community dwelling) (90%), the in-care cohort is estimated to consist of 1739 adults with an SMI. On the basis of the aforementioned proportions, the not-in-care cohort is estimated to consist of 820 people. The LZA-cohort potentially consists of 157 former LZA-participants who gave permission to be re-approached. Based on expected response rates of 33% in the in-care cohort, 20% in the not-in-care cohort and 50% in the LZA-cohort, the study sample will consist of approximately 800 participants. Figure 1 presents a flowchart depicting the composition of the study population.

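### In the two-wave mixed model, each time-dependent predictor gets one coefficient that mixes between-person and within-person associations; the time factor still estimates the trend in the outcomes

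*Protocol article*

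**What the plan says.** The instruments are "administered twice, with a two-year time interval" (Study design). The longitudinal analysis uses "generalized linear mixed models with repeated measurements of recovery, quality of life and societal participation as dependent variables" (Statistical methods). Two sentences then fix how time and the predictors enter: "The time between both measures will be included as a within-subjects factor", followed by "The same set of predictor variables as mentioned above will be treated as time-dependent independent variables". The predictors meant are those of the baseline regression described just before: the CANSAS count of unmet needs, the discrimination scale, the stigma scale and victimization. No person mean, deviation or change score is mentioned. The life-events total is added as a possible mediator of the associations between predictors and outcomes.

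On the target, the abstract states "Primary outcomes are changes over time in recovery, societal participation and quality of life". The first question listed in the Background asks which trends in quality of life, recovery, functioning and participation "can be observed over the course of time"; it names no predictor. Statistical methods assigns the mixed model to research question 3, but the third question listed in the Background asks how providers address needs. It attaches research question 1 to the baseline-only regression.

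**The concern.** With two measurements per person, a predictor such as unmet needs varies in two ways. Some people have more needs than others throughout, and some people's needs change between interviews. The first kind of variation carries all stable differences between people, measured or not. The second does not. A single coefficient on the time-dependent score pools both.

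The baseline regression already planned supplies the cross-sectional association of the same outcomes with the same predictors. What the second wave adds for these predictors is information on change, and the pooled coefficient does not show it separately. A stable difference (people with more unmet needs have poorer recovery) could then be taken as a sign that a fall in needs goes with an improvement in recovery. The same mixture carries into the step that adds life events, because that step looks at the same coefficients.

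**Working it through.** **Inputs from the document.** Two waves, two years apart. The sample statement is "the study sample will consist of approximately 800 participants", based on "expected response rates of 33% in the in-care cohort, 20% in the not-in-care cohort and 50% in the LZA-cohort". With the stated cohort sizes: 1739 × 0.33 + 820 × 0.20 + 157 × 0.50 = 573.9 + 164.0 + 78.5 = 816, in line with about 800. This figure only sets the scale of the simulation below; the point does not depend on it.

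**Assumed inputs.** The document gives no intraclass correlation (ICC) for the outcome (ICCy) or the predictor (ICCx), and no slopes. All values for these are assumptions.

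**Weights.** In a random-intercept model with two waves and one uncentred predictor:

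- coefficient = (1 − B) × within slope + B × between slope
- B = λ·Sb / (Sw + λ·Sb)
- λ = (1 − ICCy) / ((1 − ICCy) + 2·ICCy)
- Sw = (1 − ICCx)/2
- Sb = ICCx + (1 − ICCx)/2

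Mid-point, ICCy 0.5 and ICCx 0.6: λ = 0.5/1.5 = 0.333, Sw = 0.20, Sb = 0.80, so B = 0.267/0.467 = 0.57.

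Low end, ICCy 0.7 and ICCx 0.5: λ = 0.3/1.7 = 0.176, Sw = 0.25, Sb = 0.75, so B = 0.132/0.382 = 0.35.

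High end, ICCy 0.4 and ICCx 0.7: λ = 0.6/1.4 = 0.429, Sw = 0.15, Sb = 0.85, so B = 0.364/0.514 = 0.71.

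On a wider grid (predictor correlation between waves 0.3-0.8, outcome ICC 0.3-0.7), the within-person share runs from 17% to 75%. It is exactly 50% when the two correlations are equal.

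**Illustration.** With an assumed between slope of 0.40 and within slope of 0.10, the coefficient is 0.10 + 0.30·B. That gives 0.20 at B = 0.35, 0.27 at B = 0.57 and 0.31 at B = 0.71.

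**Simulation check.** 800 people, two waves, continuous outcome, ICCx 0.6, ICCy 0.5, true time effect 0.10, no shift in the predictor mean, 40 replicates per setting:

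| True within / between | Single coefficient | Split: within / between | Time effect, single / split |
|---|---|---|---|
| 0 / −0.40 | −0.235 | −0.009 / −0.398 | 0.095 / 0.098 |
| −0.10 / −0.40 | −0.272 | −0.107 / −0.398 | 0.106 / 0.106 |
| −0.30 / −0.30 | −0.296 | −0.297 / −0.295 | 0.097 / 0.097 |

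In the first row, the single coefficient was significant in all 40 replicates although no within-person association existed; the split model's within term was significant in 1 of 40 (2.5%). In the last row, with equal slopes, there is no distortion. The time effect is practically the same under both codings.

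**Measurement error in the split.** With two waves, the deviation is in effect a difference score. Its reliability is (reliability − wave correlation)/(1 − wave correlation). The protocol gives the stigma scale a test-retest reliability of .71 and an alpha of .87. With an assumed wave correlation of 0.6, this gives (0.71 − 0.6)/0.4 = 0.28 and (0.87 − 0.6)/0.4 = 0.68. Under classical error and a single predictor, the within-person slope would shrink to about 28-68% of its true value. For the person mean, the matching figure is (reliability + wave correlation)/(1 + wave correlation): 1.31/1.6 = 0.82 and 1.47/1.6 = 0.92.

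**The case against.** The strongest objection is that uncentred entry is inferred. The protocol says the predictors are time-dependent; it does not say they enter raw or with one slope each. A mean-plus-deviation coding is compatible with that sentence, and a full protocol or SAP, neither shown, might specify it. This stands as a limit on the claim. What remains is that an analyst who follows the published sentence plainly would fit one coefficient per predictor.

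A reader might infer that the model therefore fails the study's question about change over time. The document does not support that. The listed question on trends and the primary outcomes in the abstract concern changes in the outcomes, and the within-subjects time factor estimates those. One qualification applies. If the predictor means shift between waves, the adjusted time effect equals the total mean change minus the predictor coefficient times the mean shift in the predictor, so it then depends on the mixed coefficient too.

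A reader might also infer that the plan will present between-person differences as within-person change. It nowhere says so; it speaks only of associations between predictors and outcomes. Because the research-question numbers in Statistical methods do not match the list in the Background, the intended target of these coefficients is unclear. That is a reason to state the target, not evidence of a wrong one.

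Finally, the size is wholly assumed, and the split has a bias of its own through measurement error. Both objections stand and are reflected in the verdict and the fix.

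**Conclusion.** The point holds for the predictor coefficients only. As written, each is a mixture of between-person and within-person associations. Unless the two are equal, it cannot be read as a person's outcome moving when that person's needs, discrimination, stigma or victimization change. The estimated trend in the outcomes is not at issue.

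The between-person weight of 35-71% rests on the assumed ICC ranges. A reported slope two to three times the within-person value rests further on the assumed slopes of 0.40 and 0.10. The weights are derived for a continuous outcome; for the yes/no work or daytime-activities outcome the same mixing occurs with different weights. This is a worthwhile, low-cost improvement and clarification, not a flaw that invalidates the longitudinal analysis.

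**What to change.** For each time-dependent predictor, compute the person's mean over the two waves and the deviation from that mean at each wave. Enter both in the mixed model and report both coefficients. Do the same in the logistic mixed model for work or daytime activities. State in the plan which coefficient is interpreted and for which research question, and align the question numbers with the Background list. Keep the time factor as the estimate of the trend.

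The cost is one additional coefficient per predictor and no new data. The within-person coefficient will have a wider interval, which reflects how much information two waves hold on change. It will also be attenuated by measurement error, more strongly than the between-person one. It should therefore be shown beside the between-person coefficient with that caveat, and a gap between the two should not by itself be read as proof of confounding. A participant with only one interview has a deviation of zero and informs only the between-person coefficient, so the number of people contributing to each should be given.
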